**Figure 4. F4:**
[figure not shown]
TBI (traumatic brain injury)-AD/ADRD (Alzheimer disease and related dementias) caregiver support intervention (TACSI) map. AD: Alzheimer disease.

###### Dementia and TBI Education (Addressing Objective 1)

To increase understanding of AD/ADRD and TBI, coaches share how TBI and dementia affect the brain and how that may impact behavior, personality, and cognition. This education provides an explanation and foundation for the caregiver to understand why the relative may be functioning as they are and how they may be impacted in the future. Learning that their care recipient’s behavior is not an intentional choice, but a result of the injury or disease process, can help reduce the annoyance some caregivers may experience. It also helps them to have appropriate expectations and to make plans for the future. In addition, the intervention shares approaches that help to prevent and better manage frustrating behavior (eg, aggression, wandering, hygiene avoidance). Education also focuses on processing and addressing uncomfortable role changes that the caregiver may be experiencing, including adjusting to new responsibilities and changes in spousal intimacy.

###### Promoting Stress Management and Well-Being (Addressing Objectives 2 and 3)

The intervention aimed to help improve mood and manage stressors. Exploration of the caregiver’s experiences with guilt and grief sought to help identify sources of negativity and subsequently, process, validate, normalize, and reframe those negative emotions. Stressors were identified, including those related to caregiving, as well as outside sources of stress. Stress management techniques, including relaxation exercises and problem-solving strategies, such as breaking a larger problem into smaller tasks and setting specific, measurable, achievable, relevant, and time-bound goals, were explored. The caregiver’s experience with loneliness and social isolation was explored, along with the importance of self-care and social engagement.

###### Enhancing Communication (Addressing Objective 4)

Coaches focused on providing a range of communication skills and strategies for caregivers to use with their care recipients, families, health care teams, and others. Through psychoeducation on the tenets of effective communication and the sharing of conflict resolution strategies, the intervention aims to help caregivers convey their perspective, gain understanding and support from others, and advocate for their care recipient. Coaches also offer approaches on how to best engage with a health care team, adapted from the Health Resources and Services Administration’s “Working with a Healthcare Team” module [59]. Additionally, coaches share strategies to improve communication and engagement with the care recipient.

###### Building Awareness of Supports (Addressing Objectives 5 and 6)

Caregivers learn about the local and national supports and services that can meet their unique needs. Provision of these personalized local and national formal supports is complemented by the identification of sources of informal support, such as family, friends, and neighbors. Once these informal sources of support are identified, coaches process caregiver reservations about asking for assistance, provide guidance, and encourage caregivers to ask for and accept offers of help and respite.

### Ad Hoc Sessions

Ad hoc sessions, delivered via telephone, secure web conferencing, or email, were available at any time between sessions and following intervention completion. Caregivers could schedule a standing ad hoc session or request impromptu ad hoc coaching. Ad hoc sessions and email consultations were unstructured and designed to address any caregiver concerns in a timely manner.

### Interventionist Characteristics

The program is designed to be delivered by a qualified coach based on education or training. Recommended qualifications include: (1) a Bachelor’s degree or higher in a health or wellness-related field; (2) relevant experience working with people with memory loss or their caregivers; (3) experience or proficiency in remote intervention delivery, particularly having the ability to establish rapport without being in person; and (4) completion of TACSI training based on the intervention manual. See Table 2 for additional interventionist characteristics [46].

TACSI coaches were 2 doctorally educated staff (DNP and PhD in clinical psychology). Both have personal and professional experience with individuals with dementia and their caregivers, as well as experience with remote intervention delivery. The coaches worked together previously on ADRD caregiving studies. Similar procedures were used in this study as in the previous intervention studies.

The coach-developed (RB) intervention includes a manual that specifies the procedures for delivering the intervention and details module content. The manual serves as a guide on intervention structure, delivery processes, and session content. Coach training consisted of a thorough step-by-step review of the treatment manual, including discussion of appropriate question prompts, how to start topic discussions, and how to tailor the content to the individual participant. Coaches meet regularly to discuss the intervention, problem-solve any concerns, and share information and newly discovered resources. Coinvestigator JF, a MVAHCS staff psychologist, was present at weekly meetings throughout study recruitment and was available to confer with coaches on any issues as needed.

### Data Collection and Measures

#### Overview

Data collection for both treatment and control groups was conducted via surveys. Additional data were collected from treatment group caregivers via TRCs and semistructured interviews.

#### Surveys

Caregivers received a baseline survey collecting information on sociodemographics, context of care, and outcome measures. The baseline survey contained sociodemographic measures for both the caregiver and care recipient (date of birth, gender, racial background, marital status, education level, and household income). Context of care variables, such as geographic location, caregiver work status, health conditions, and relationship to care recipient were assessed. Additional variables included year and severity/type of TBI and AD/ADRD diagnoses with concurrent symptoms, care recipient Veteran and Medicaid status, and living arrangement.

Two follow-up surveys were administered by a research assistant blinded to participant group assignment from randomization through the end of analysis. The first follow-up (T1) was administered at 3 months post completion of the baseline survey; the second follow-up was administered 3 months after completion of the 3-month survey (T2). If a care recipient passed away during the study, modified bereavement surveys were administered at follow-up.

Three options for completing surveys were offered: online via Qualtrics, a mailed survey, or over the phone with study staff. The specific measures selected for assessment have strong psychometric properties; Table 1 displays outcome measures administered by time point and survey type. Primary outcome measures assessed perceived burden, caregiver relationship satisfaction, caregiving ideology, and caregiving mastery using the Modified Caregiver Appraisal Scale [36]. Secondary outcome measures evaluated caregiver well-being via the Center for Epidemiological Studies-Depression Scale [37] and multiple TBI caregiver quality of life [38] subscales assessing feelings of loss, feeling trapped, caregiver anxiety, strain, vigilance, emotional suppression, and family disruption. Secondary outcome measures also evaluated caregiver resource usage, including hospital and residential care service use and community-based services such as housekeeping [39], caregiver personal resources (coping style [40], interpersonal supports [41], and self-efficacy [42]), ADLs/instrumental activities of daily living [43,44], and care recipient behaviors [45].

Adverse events were defined prior to the onset of the study, and standardized procedures were determined to address these events, if encountered. At the 3 and 6 month follow-up timepoints, participants were asked: “In the last three months, since your last survey, was there any new or worsening health problem that caused you to be unable to perform your daily routine (ie, not go to work or volunteer), seek medical care (ie, go see your doctor, go to the ER or hospital), or take a new medication?” Those medical events were documented as adverse events. In addition, during each intervention session, coaches inquired into and addressed participant health and other concerns, as applicable.

Staff provided up to 4 reminders to complete each survey via phone or email. If a follow-up survey was not completed, subsequent surveys were still sent unless the participant withdrew from the study. Staff provided a thank-you phone call or email after completion of each survey.

#### Treatment Receipt Checklist

Within 2 weeks of the completion of their follow-up surveys (T1, T2), treatment group caregivers were sent an additional survey by an unblinded staff member to evaluate treatment receipt via a brief TRC, as well as assess the acceptability, appropriateness, and feasibility of the intervention. Unblinded staff provided reminders to complete the TRCs; thank you emails or calls were completed following survey completion.

The TRC is a 13-item survey evaluating participant receipt of various components of the intervention using 12 Likert scale items (1=strongly disagree to 5=strongly agree, with an option for not applicable/does not apply to me). An open-ended question inquiries about how TACSI was or was not helpful (Wilson et al [29] provides TRC items).

Acceptability, appropriateness, and feasibility of the intervention were evaluated using the acceptability of intervention measure (AIM), the intervention appropriateness measure (IAM), and the feasibility of intervention measure (FIM) [60]. Each measure consists of 4 items using a 5-point Likert scale (1=completely disagree; 5=completely agree). These measures demonstrate strong validity, high internal consistency (AIM, α=.85; IAM, α=.91; and FIM, α=.89), and high test-retest reliability (AIM=0.80, IAM=0.73, FIM=0.88).

#### Bereavement or Residential Placement

If the care recipient passed away during the study, the participating caregiver was offered condolences by the staff. Pending their willingness to continue the study, these caregivers were administered modified bereavement surveys at follow-up. If the caregiver was in the treatment group, they no longer participated in standard TACSI sessions. However, the interventionist offered optional ad hoc sessions focused on the participant’s needs, integrating TACSI content only if relevant. Depending on the number of study time points remaining, either one or two bereavement surveys would be administered, both omitting measures no longer applicable, as shown in Table 1.

In the case of a care recipient’s nursing home admission, the caregiver could continue study involvement (TACSI intervention and routine follow-up surveys) as usual.

#### Semistructured Interviews

Twenty participants in the treatment group were purposely selected to participate in an audio-recorded semistructured interview to provide qualitative data regarding the TACSI program. Staff selected participants who rated TACSI with higher and lower average scores on the TRC and measures assessing the intervention’s appropriateness, acceptability, and feasibility (see above). Additionally, as the sample allowed, the study team made an effort to select participants with varied characteristics: relationship to care recipient (partner, adult child), severity of condition (TBI-AD/ADRD), and racial/ethnic identity. Participants could complete the semistructured interview via phone or secure video conferencing (Zoom). Multimedia Appendix 2 contains the interview guide.

#### Coach Documentation

Throughout each caregiver’s time in the study, coaches documented any participant contact for treatment and control participants: dates, method of contact, length of contact, and general topics of discussion. Session notes were also completed by coaches, documenting key issues, family dynamics, participant response or engagement with session content, and plans for the next session’s content.

### Analysis

Quantitative analysis will include descriptive statistics, such as frequency tables and means, to describe sample characteristics and TBI-AD/ADRD caregiver outcomes. Enrollment and recruitment data, such as the number of contacts or referrals by site, reasons for exclusion, and retention, will be summarized. Distribution/normality and missing data will also be examined.

The number of TBI-AD/ADRD caregivers enrolled to address the study hypotheses (n=80) was determined using power analysis procedures that relied on Wänström’s Monte Carlo simulations [61]. A final sample of 72 TBI-AD/ADRD caregivers was found sufficient for detecting a medium effect size of 0.5 at a statistical power level of 0.8, while adjusting for 10% loss to follow-up and for multiple potential statistical differences between treatment and control groups at baseline. In order to evaluate whether a full-scale randomized controlled design is feasible and appropriate, we will conduct paired *t* tests to determine whether the TACSI treatment and control groups are statistically (*P*>.05) equivalent across all baseline outcomes and TBI-AD/ADRD caregiver covariates. Multilevel regression analyses of outcome and growth curve modeling will be used to compare rates of change between the treatment and control groups in primary subjective stressors and other caregiver outcomes. The primary independent variable will indicate random assignment into the TACSI treatment or control group. If any sample characteristics or outcomes vary significantly at baseline between the treatment and control groups, the baseline values will be included as covariates. In order for the intercept effect to be a main effect and to have a treatment*time interaction effect, the baseline value of each outcome will be a covariate, and time will be centered at 3 months after the baseline survey. We will explore whether treatment participants experienced statistically significant (*P*<.05) declines in primary subjective stress, increased well-being, and other changes in TBI-AD/ADRD caregiver outcomes when compared with controls over the study period. Further, Cox proportional hazard models will be run with the events including admission to a nursing home, assisted living, similar residential living situation, and emergency department and overnight hospital stays.

We will calculate means and create frequency tables to evaluate AIM, IAM, and FIM measures and TRC at T1 and T2. We will determine if 80% of treatment caregivers found the intervention appropriate, feasible, and acceptable at the 2 follow-up timepoints (T1 and T2).

Post hoc analyses will also be conducted. Specifically, to examine the effects of TACSI use on changes in primary subjective stress and caregiver well-being, intervention session data regarding variations in use of TACSI, such as frequency and duration of counseling sessions, will also be included in the growth curve models.

The qualitative analysis will use reflexive thematic content analytic techniques as described by Morse, Moser, and others [62-66]. The semistructured interviews and open-ended comments from the TRCs will comprise the qualitative data. The research staff will read the qualitative data to familiarize themselves with the data and make changes to the Phase I codebook accordingly. Staff will review and discuss coding assumptions before making any revisions to the codebook. This qualitative analysis will help determine why TACSI did or did not meet the needs of TBI-AD/ADRD caregivers.

The mixed methods analysis aims to provide empirical context for the participants’ perceptions of TACSI. A sequential mixed methods sampling approach was used in selecting treatment participants for the semistructured interviews. This will enable research staff to better understand participants’ perceptions of TACSI’s usefulness while also linking qualitatively derived themes with the outcome data. Specifically, the empirical outcome data will be sorted by qualitative themes that appeared across the 2 subgroups of the semistructured interview sample (those who rated TACSI as highly acceptable, feasible, and useful in the TRCs vs those who rated TACSI poorly on the same measures). This mixed methods approach will allow us to determine if certain themes appear more often for one subgroup than the other subgroup, or if the subgroups use TACSI recommendations differently.

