**Methods:**

This pilot RCT uses an embedded mixed methods randomized controlled evaluation. Caregivers of individuals with a dual diagnosis of AD/ADRD and a history of TBI are randomly assigned to the TACSI (n=41) or a usual care control condition (n=39). Primary outcomes include perceived burden, caregiver relationship satisfaction, and caregiving mastery. Secondary outcomes include caregiver self-efficacy, well-being, and personal resources. Qualitative elements (up to 20 semistructured interviews at the conclusion of the 6-month evaluation and an open-response item at follow-up surveys) allow for better interpretation of quantitative results and understanding of TACSI’s mechanisms of benefit.

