### Design

This embedded experimental mixed methods study used a pilot RCT design to determine the feasibility and performance of TACSI with 80 caregivers of persons with TBI-ADRD. The mixed methods approach integrated elements of quantitative and qualitative data collection at multiple time points throughout the study for a more robust analysis, enriching our understanding of the caregiver experience in comparison to solely collecting qualitative or quantitative data (Figure 1) [31,32].

Inclusion of qualitative data provides pertinent context for interpretation of quantitative results and rich insight into the intervention’s mechanisms of benefit [33,34]. The mixed methods pilot RCT design allowed for the evaluation of appropriateness and sufficiency of the recruitment, screening, randomization, treatment receipt, and retention processes (all appropriate pilot RCT goals over a 6-month follow-up period) [35].

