#### Randomization Procedures

After baseline survey completion, participating caregivers were randomly assigned on a 1:1 basis to participate in either (1) the TACSI program treatment group or (2) the usual care control group (the latter continued routine care through their HCS). The random assignment schedule was created digitally by a staff member involved in the study solely for this task, via Research Randomizer. Participants had equal chances of being assigned to either the treatment or control group. The assignment schedule was input into a series of sequenced envelopes to be opened in order at the time of randomization (following a participant’s baseline survey completion).

The study coordinator informed participants about the results of their randomization to either the TACSI treatment group or the usual care control group via phone, email, or both. Coordinators also alerted the TACSI study coaches, who divided the participant caseload based on workload and availability. Those in the control group were given the opportunity to request resources or referrals during their randomization notification and as a part of the survey completion thank you procedures in order to provide support and bolster retention.

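### Paired t tests with P>.05 across baseline variables cannot show that two independent randomised arms are equivalent or that a full-scale RCT is feasible

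*Protocol article*

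**What the plan says.** The Analysis section introduces the baseline comparison with a purpose, "In order to evaluate whether a full-scale randomized controlled design is feasible and appropriate", and then names the test and criterion: "we will conduct paired *t* tests to determine whether the TACSI treatment and control groups are statistically (*P*>.05) equivalent across all baseline outcomes". The scope extends to covariates: "statistically (*P*>.05) equivalent across all baseline outcomes and TBI-AD/ADRD caregiver covariates". No equivalence margin is given.

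The same section uses baseline significance a second time. Characteristics or outcomes that differ significantly between arms at baseline are added to the outcome models as covariates. Separately, the baseline value of each outcome is always a covariate in its own model.

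Under Randomization Procedures, "participating caregivers were randomly assigned on a 1:1 basis", with no matching described. The abstract gives the arm sizes: caregivers "are randomly assigned to the TACSI (n=41) or a usual care control condition (n=39").

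Other feasibility information is planned. The Design section says that the pilot "allowed for the evaluation of appropriateness and sufficiency of the recruitment, screening, randomization, treatment receipt, and retention processes". The Analysis section summarises enrolment, exclusions and retention. It also sets an 80% target for treatment caregivers finding the intervention appropriate, feasible and acceptable at T1 and T2.

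**The concern.** The rule has three separate faults.

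- **The test does not fit the design.** A paired t test needs a natural partner in the other arm for each caregiver, and there is none. Several listed covariates (gender, racial background, marital status, relationship to the care recipient) are categorical, so neither a paired nor an independent-samples t test suits them.
- **The criterion does not show what it claims.** Failing to reject a null hypothesis of no difference is not a demonstration of equivalence, least of all with about 40 per arm and no margin.
- **The result does not answer the question put to it.** With proper randomisation, baseline differences arise by chance. Their P values do not tell the team whether a larger trial could recruit, deliver and retain.

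At stake is a main conclusion of the pilot. This is the only analysis that the Analysis section introduces explicitly as evaluating whether a full-scale randomised design is feasible and appropriate. It could give a false alarm from chance differences, or a false reassurance of balance. Through the covariate rule, chance results could also change which variables enter the outcome models.

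**Working it through.** **Inputs from the protocol article**

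- Arm sizes: 41 and 39 (abstract).
- Threshold: .05 (Analysis). Two-sided testing is assumed.
- Baseline outcomes, counting each measure in Table 1 once. There are four primary subscales: "Primary outcome measures assessed perceived burden, caregiver relationship satisfaction, caregiving ideology, and caregiving mastery using the Modified Caregiver Appraisal Scale". The others are depression 1, TBI-CareQOL forms 8, service use 2, coping 1, interpersonal support 1, self-efficacy 1, ADL/IADL 1 and care-recipient behaviour 1. Total: 4 + 1 + 8 + 2 + 1 + 1 + 1 + 1 + 1 = 20.
- Caregiver covariates (Surveys section): six sociodemographic items and at least four context-of-care items, so about 10.
- Correlation among baseline outcomes: not given. It is assumed to be common to all pairs and varied from 0 to 0.7.

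The plan states no figure for this rule, so there is none to reproduce.

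**Step 1. Can the test be formed?** With 41 and 39 unrelated people there are no pairs. A paired test would need arbitrary matching and would leave at least two caregivers out.

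**Step 2. What does P>.05 let through?** For an independent-samples t test, the smallest significant observed difference in SD units is t(.975, 78) × √(1/41 + 1/39) = 1.991 × 0.2237 = 0.445. Any observed difference below about 0.45 SD passes as equivalent.

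**Step 3. Would a formal equivalence test rescue the idea?** Take two one-sided tests at .05, a true difference of zero and the normal approximation. The power is 0% at a margin of 0.3 SD and 45% at 0.5 SD. For 80% power the margin must be (1.282 + 1.645) × 0.2237 = 0.65 SD, which exceeds the 0.5 effect size that the trial is designed to detect. Changing the test would not make this a useful criterion.

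**Step 4. How often does a correctly randomised trial show at least one P<.05?** For k independent tests the probability is 1 − 0.95^k.

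- k = 20 (outcomes only): 1 − 0.95^20 = 64%.
- k = 30 (outcomes plus 10 covariates): 1 − 0.95^30 = 79%, with 30 × 0.05 = 1.5 chance differences expected.

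For correlated outcomes, p is the simulated probability of at least one P<.05 among 20 equally correlated normal outcomes, 41 versus 39, with no true difference. Adding 10 independent covariates gives 1 − (1 − p) × 0.95^10, where 0.95^10 = 0.599.

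| Outcome correlation (assumed) | 20 outcomes only | Plus 10 covariates |
|---|---|---|
| 0 | 64% | 79% |
| 0.2 | 59% | 76% |
| 0.4 | 49% | 69% |
| 0.5 | 42% | 65% |
| 0.7 | 29% | 58% |

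For the four primary subscales alone, the probability is about 16% to 19% with correlations of 0.5 to 0.

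**The case against.** Several points on the other side have force.

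- **Feasibility does not hang on this test alone.** A reader might infer that it does. The Design and Analysis sections show otherwise: recruitment, screening, randomisation, treatment receipt and retention are all to be evaluated, and there is an 80% target. The tests carry part of the judgement.
- **No fail rule is stated.** A reader might infer that one significant variable means a full-scale trial is declared infeasible, so that a sound trial would usually fail. The documents do not say so. The only stated consequence of a significant difference is covariate adjustment. The percentages in Step 4 apply only if the criterion requires every variable to pass. On the 20 outcomes alone they fall below 50% once the correlation reaches about 0.4.
- **Higher figures need more variables.** Forty independent tests would give 1 − 0.95^40 = 87%. Reaching 40 means counting care-recipient variables, whereas the text refers to caregiver covariates.
- **A miss rate for a true imbalance does not belong here.** Valid randomisation excludes a true population difference at baseline. The defensible statement concerns observed differences, as in Step 2.
- **Baseline comparison has some use.** It can serve as a weak check that allocation was carried out as intended, which is one of the processes under evaluation. Descriptive comparison serves that purpose without a P>.05 verdict.
- **The word paired may be a slip** for independent-samples or pairwise. If so, one word repairs the mismatch with the design. The categorical covariates, the equivalence claim and the link to feasibility remain wrong.
- **The outcome models are largely protected.** Each already includes its own baseline value, whatever these tests show. Only the conditional addition of other covariates depends on them.

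**Conclusion.** The concern holds in a limited form. As written, the test does not apply to the design, the P>.05 criterion cannot show equivalence, and the result does not inform whether a full-scale trial is feasible. These are errors in what the text states, not details left to an analysis plan.

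The threshold for a significant observed difference, about 0.45 SD, follows from the arm sizes and two-sided testing at .05. The 58% to 79% range for at least one chance finding rests on three assumptions: all variables must pass, there are about 20 outcomes and 10 independent caregiver covariates, and the outcome correlations lie between 0.7 and 0. For outcomes alone the range is about 29% to 64%.

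This should be fixed. It is not graded higher because the plan already contains better feasibility measures and states no automatic decision from these tests.

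**What to change.** Four changes to the Analysis section:

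1. Delete the paired t tests and the P>.05 equivalence criterion.
2. Describe baseline characteristics and outcomes by arm, with standardised differences and no P values.
3. Replace the rule that adds covariates according to baseline significance with a short prespecified set, alongside the baseline value of each outcome that is already planned. Without this change, deleting the tests would leave a rule that depends on them.
4. State that the conclusion about a full-scale RCT rests on the recruitment, screening, randomisation-process, treatment-receipt and retention data and on the 80% target for acceptability, appropriateness and feasibility.

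The cost is analysis wording only, with no new data. The article reports data collection as complete and analysis as still to follow. The covariate set should therefore be fixed before outcomes are examined by arm, and the change recorded with its date.

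### Covariates beyond each outcome's own baseline value are chosen by baseline significance tests, which pick chance imbalances rather than predictors and cost some precision

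*Protocol article*

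**What the plan says.** Three statements in the Analysis section of the protocol article bear on this.

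- The arms are to be tested at baseline to see whether they are "statistically (*P*>.05) equivalent across all baseline outcomes and TBI-AD/ADRD caregiver covariates".
- What differs is then adjusted for: "If any sample characteristics or outcomes vary significantly at baseline between the treatment and control groups, the baseline values will be included as covariates".
- The next sentence fixes one covariate unconditionally: "the baseline value of each outcome will be a covariate, and time will be centered at 3 months after the baseline survey".

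The candidates come from the Surveys section. It lists six sociodemographic items for both caregiver and care recipient, and further items: "Context of care variables, such as geographic location, caregiver work status, health conditions, and relationship to care recipient were assessed". Table 1 adds about 20 baseline outcome scales. The Randomization Procedures section describes 1:1 assignment and no stratification factor. No covariate other than the outcome's own baseline value is named in advance.

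**The concern.** Assignment is random, so a significant baseline difference is a chance event. The test measures how far the arms happen to differ. It carries no information on whether the variable predicts burden, relationship satisfaction, ideology or mastery. Three consequences follow.

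- A strong predictor enters the model no more often than a useless one.
- Each flagged variable is by construction correlated with arm. If it does not predict outcome, including it widens the standard error of the treatment effect and gives nothing back.
- The covariate set of the primary models is unknown until baseline data have been compared by arm.

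The two adjacent sentences also disagree about outcomes. One includes their baseline values only if the arms differ; the other always includes them. The first can be read as adding the baseline values of other outcomes to each model, with about 72 caregivers analysed.

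**Working it through.** **The plan's own figure.** The article states: "A final sample of 72 TBI-AD/ADRD caregivers was found sufficient for detecting a medium effect size of 0.5 at a statistical power level of 0.8". The dropout step reproduces: 72/0.9 = 80. For a plain two-sided comparison at 36 per arm, power is Φ(0.5 × √(36/2) − 1.96) = Φ(0.16) = 0.56. The stated 0.8 must therefore draw on baseline adjustment and repeated measures. It is attainable (ANCOVA on the mean of two follow-ups at correlation 0.3 gives 0.81), but the correlation inputs are not given, so it is neither confirmed nor refuted. Precision from adjustment clearly matters here.

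**How many variables are flagged.** The count is an assumption: 6 items × 2 people = 12, plus about 8 to 12 context items, plus about 20 scales. I use 20 to 40 tests, two-sided at 0.05.

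- Expected flags: 20 × 0.05 = 1 and 40 × 0.05 = 2.
- Chance of at least one, if independent: 1 − 0.95^20 = 0.64 and 1 − 0.95^40 = 0.87. Correlation among candidates lowers this chance but not the expected number.

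**What is missed.** With 41 v 39, the cut-off is 1.99 × √(1/41 + 1/39) = 0.445 SD. A predictor with a smaller imbalance stays out, however prognostic it is.

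**What a flagged variable costs.** At the cut-off, its squared correlation with arm is 1.99²/(1.99² + 78) = 0.048. If it does not predict outcome, the variance of the treatment estimate rises by a factor of at least about 1/(1 − 0.048) = 1.05.

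**Simulated power.** ANCOVA on one follow-up stands in for the growth model: 36 per arm, effect 0.5 SD, 20 independent candidates of which one is prognostic, own baseline always included, 4,000 trials per row. Correlations and coefficients are assumptions.

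| Baseline correlation | Predictor coefficient | Plan's rule | Own baseline only | Predictor fixed in advance |
|---|---|---|---|---|
| 0.5 | 0.2 | 0.64 | 0.67 | 0.69 |
| 0.5 | 0.3 | 0.65 | 0.67 | 0.73 |
| 0.5 | 0.4 | 0.64 | 0.66 | 0.76 |
| 0.7 | 0.2 | 0.80 | 0.83 | 0.85 |
| 0.7 | 0.3 | 0.81 | 0.83 | 0.89 |
| 0.7 | 0.4 | 0.82 | 0.84 | 0.94 |

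The prognostic variable was selected in about 5% of trials. At correlation 0.5 and coefficient 0.3, the mean standard error is 0.235 with no adjustment, 0.205 with own baseline only, 0.212 under the rule and 0.193 with the predictor fixed. With no true effect, the rule rejected in 4.3% to 4.5% of trials.

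**More candidates, and a list of three covariates.** These runs use 37 v 35, correlation 0.5 and 20 to 40 candidates.

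- Against own baseline alone, the rule loses about 2 to 7 points.
- Three fixed covariates v the rule, none prognostic: 0.64 to 0.66 v 0.59 to 0.64.
- One of the three prognostic at 0.3: 0.69 to 0.71 v 0.61 to 0.63.
- One of the three prognostic at 0.5: 0.81 to 0.82 v 0.61 to 0.63, a gap of up to about 20 points.
- Three fixed covariates v own baseline alone: 0.651 v 0.665 at coefficient 0.1, 0.676 v 0.672 at 0.2 and 0.708 v 0.674 at 0.3. If none is prognostic, the list loses about 2 points.

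**The case against.** The strongest reply is that the plan already secures what matters most. The outcome's own baseline value is usually its best predictor, and it enters every model. A reader might infer from the significance rule that all adjustment hangs on the baseline test and that nearly all the precision gain is lost. The document does not support that: the next sentence is unconditional, and it accounts for the fall in standard error from 0.235 to 0.205 in the illustration. This part of the reply stands and limits the point to the additional covariates.

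A reader might also infer that a data-dependent model biases the result or inflates false positives. Selection uses baseline data and arm, not outcomes, and the threshold is stated. Simulated type I error stayed at or slightly below 5%, so that inference fails too.

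The sample size is said to be set "while adjusting for 10% loss to follow-up and for multiple potential statistical differences between treatment and control groups at baseline", so extra covariates were foreseen. That allowance is not quantified, however, and does not make the choice of covariates a good one.

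Finally, nothing in the article shows which variables predict these outcomes, so a fixed list may gain little. This stands in part. With weak predictors the list is level with, or slightly below, own-baseline adjustment alone. It still did better than the plan's rule at every strength tried.

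Pilot status does not remove the point, because the plan tests for "statistically significant (*P*<.05) declines in primary subjective stress" against controls and the results inform a full-scale trial.

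**Conclusion.** The point holds for covariates other than the outcome's own baseline value. It concerns efficiency and pre-specification, not validity. The rule costs about 2 to 7 power points against own-baseline adjustment alone, and about 2 to 20 against a short fixed list. The low end of the second range applies when no listed covariate is prognostic, the high end when one has a partial coefficient of 0.5.

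These sizes rest on assumptions the article does not supply: 20 to 40 independent candidates, a baseline correlation of 0.5, predictor coefficients from 0 to 0.5, and a single-follow-up ANCOVA in place of the growth model. The direction is firmer than the size, because under proper randomisation a baseline significance test cannot separate predictors from noise.

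**What to change.** Delete the significance rule. State that every model includes the outcome's own baseline value. Before arm-level data are examined, name two or three likely predictors already collected at baseline and use them whatever balance is observed. Candidates include relationship to care recipient, recruitment source and the baseline care-recipient behaviour score; the choice is the investigators' judgement, since the article does not show their prognostic strength. Label any further adjustment as a sensitivity analysis. Baseline differences can still be described.

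This also removes the conflict between the two adjacent sentences on outcome baselines. The article reports data collection as complete with analysis to follow, so the change is one of wording. It costs two or three degrees of freedom and, if none of the chosen covariates is prognostic, about 2 power points against own-baseline adjustment alone.
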